### Third aim: Functional outcomes

Quality of life will be evaluated using the short form-36 (SF 36) [53, 54].The Functional Independence Measure (FIM) [55] will be used to evaluate functional independence in eighteen motor and cognitive domains. The FIM can be used to follow change from the beginning of rehabilitation to discharge [56]. The ABILOCO scale (a measure of locomotor ability for adults) [57] will be used to be assess locomotor ability. The test rates the individual’s ability to move about effectively in his/her environment by the evaluation of thirteen tasks including simple and complex movements. The scale is sensitive to changes in walking ability [12].The ABC scale (Activities Balance Confidence) will be used assess confidence in carrying out sixteen activities of daily living both indoors and outdoors [58].

### Management of adverse events

Patients will be informed about possible adverse events at the time of inclusion. If any adverse events occur, the study coordinator must be immediately contacted. Two types of adverse events will be considered.

Non-serious adverse events or effects are defined as any harmful manifestation that occurs in the subject, whether or not this manifestation is linked to any experimental element of the research or products used. Non-serious events may include: pain or burning at the injection site, injected limb pain, ecchymosis, hypertonia, muscular weakness, arthralgia, asthenia, hyperesthesia, pain, depression, insomnia, discomfort, nausea etc.

Serious adverse events or effects are any adverse event or effect that results in death, endangers life, requires hospitalization or prolongation of hospitalization, causes significant or lasting disability, or results in an anomaly or a congenital malformation. Undesirable effects whose nature, severity or evolution does not correspond to the information contained in the references recognized by the authorities are considered as serious, as are any adverse effects related to the diffusion of the BTX-A away from the injection site. Serious adverse events therefore include excessive muscle weakness, dysphagia, inhalation pneumonia, anaphylactic reactions etc.

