#### Analysis of safety criteria

The number and percentage of patients who experience adverse expected or unexpected effects, as well as serious adverse effects relating to the active treatment will be analysed. The nature of each effect will be specified. The duration and percentages of any adverse effects following BTX-A injection will be compared with any that occur following placebo injection using non-parametric tests.

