## Discussion

We expect that BTX-A injection in the RF and TS muscles will increase their length and peak lengthening velocity and decrease peak muscle force during gait 1 month, and perhaps also 3 months, after the injection. We expect to find a reduction in the spasticity of these muscles, an increase in passive knee flexion and passive ankle dorsiflexion, a decrease in knee extensor and plantarflexor muscle strength (MRC scale, and isokinetic dynamometer) and a reduction in force generated by these muscles during gait (SIMM model) in the BTX-A group. The peak force couple produced by the knee flexors/extensors during active movements (measured on the isokinetic dynamometer) should decrease, and the angle at which peak force occurs during passive movements should increase, demonstrating a decrease in spasticity. We also expect spatiotemporal gait parameters to improve, with an increase in gait velocity, cadence and stride length. Peak ankle dorsiflexion in stance and perhaps also in swing, and peak knee flexion in swing should increase. Peak plantar flexion moment in pre-swing phase may decrease. Based on the results of the pilot study by Lampire [15], we hypothesise that the length and lengthening velocity of the injected muscles will improve 1 month post injection.

We anticipate that these changes (particularly 1 month after BTX-A injection) will be associated with a concomitant increase in gait velocity during the 10-MWT and distance walked during the 6MWT, and reductions in performance time of the stairs and Timed Up and Go tests.

This is the first randomised, placebo-controlled trial using instrumented measures, such as 3D gait analysis and an isokinetic dynamometer, to evaluate the effects of BTX-A on gait parameters and force in patients with chronic stroke-related hemiparesis. We expect improvements of all the parameters studied in the BTX-A group. In contrast, we do not expect any significant improvement of any outcome measures in the placebo group.

Analysis of correlations between the different results will reveal if changes in the biomechanical properties of the injected muscles are related to improvements in kinematic and kinetic parameters and functional tests.

The results of this study will therefore increase understanding of the results of many previous un-controlled studies that have found improvements in kinematic parameters following BTX-A injection in patients with chronic hemiparesis.

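### Unexpectedness alone makes an effect serious, so the planned count of serious effects does not measure seriousness alone

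*Protocol article*

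**What the plan says.** The section Management of adverse events sets up a two-way split: "Two types of adverse events will be considered". The serious class begins with outcome criteria: "Serious adverse events or effects are any adverse event or effect that results in death, endangers life, requires hospitalization or prolongation of hospitalization", followed by significant or lasting disability and congenital anomaly. Two further routes into the class are then added. The first concerns effects whose nature, severity or course "does not correspond to the information contained in the references recognized by the authorities are considered as serious". The second concerns distant spread: "as are any adverse effects related to the diffusion of the BTX-A away from the injection site". Neither carries a condition on outcome.

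The other class opens with "Non-serious adverse events or effects are defined as any harmful manifestation that occurs in the subject", whether or not it is linked to the research, and gives a list of mostly mild examples. The same section requires immediate contact with the study coordinator for any adverse event.

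The section Analysis of safety criteria plans the number and percentage of patients with "adverse expected or unexpected effects, as well as serious adverse effects relating to the active treatment". It adds that the nature of each effect will be specified. It then plans a non-parametric comparison of BTX-A with placebo on the duration and percentages of any adverse effects.

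**The concern.** Seriousness describes what an event led to. Expectedness describes whether the reference information already covers it. An effect can have either property without the other. The safety analysis respects this by naming expected or unexpected effects and serious effects as different things to report. The definition does not: it makes unexpectedness sufficient for seriousness.

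At stake is the meaning of one planned safety figure. A reader of the trial report will take a percentage of patients with serious effects to mean death, danger to life, hospitalisation, disability or malformation. Under the written rule it would also include trivial effects that are merely unlisted, and the figure would not show in what proportion.

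**Working it through.** The article states no safety rate, margin or safety power, so there is no figure to reproduce. The check is of the text, followed by an illustration of size.

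**Text**

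1. The unexpectedness rule names nature, severity or evolution as alternatives. A mismatch in nature alone is enough, so an effect of a kind not listed in the reference information is serious however mild or short it is.
2. The rule is worded for effects, and the safety analysis counts patients with effects. The rule therefore feeds directly into the planned number and percentage.
3. The safety analysis lists expectedness and seriousness side by side. Under the definition, every unexpected effect is also a serious one, so the serious count contains the whole unexpected count.
4. The rule only adds to the class. Every event that meets an outcome criterion remains serious, so none is lost.

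**Size (illustration only)**

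Inputs:
- *s*, the share of patients meeting an outcome criterion. This is assumed, from 2% to 10%.
- *u*, the share with an unexpected effect that meets no outcome criterion. This is assumed, from 5% to 20%, and taken as independent of *s*.
- 20 patients per arm: the forty planned in Sample size calculation, assuming equal arms.

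Reported serious share: r = 1 − (1 − s)(1 − u).
Share of those patients who meet no outcome criterion: (r − s)/r.

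With s = 5%:

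| u | r | (r − s)/r | expected serious patients per 20 |
|---|---|---|---|
| 0% | 5.0% | 0% | 1.0 |
| 5% | 1 − 0.95 × 0.95 = 9.75% | 4.75/9.75 = 49% | 1.95 |
| 10% | 1 − 0.95 × 0.90 = 14.5% | 9.5/14.5 = 66% | 2.9 |
| 20% | 1 − 0.95 × 0.80 = 24.0% | 19.0/24.0 = 79% | 4.8 |

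Over the full assumed range, the share meeting no outcome criterion runs from 31% (s = 10%, u = 5%: 4.5/14.5) to 91% (s = 2%, u = 20%: 19.6/21.6). For a single patient, one mild unlisted effect in someone not otherwise counted adds 1/20 = 5 percentage points to that arm's serious percentage. Effects of distant spread are not included in these figures and could add to them.

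**The case against.** Several points on the other side stand.

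- **Arm comparison.** A reader might infer that the mixed definition biases the test between arms. The only test the article names covers any adverse effects, and moving an effect between classes leaves that test unchanged. Serious effects appear only as a number and percentage.
- **Overlapping classes.** A reader might infer that events will be counted twice, because the non-serious definition taken literally also covers a fatal event. With two types announced and mild examples given for the first, the natural reading is that non-serious is the remainder. No non-serious table is planned, so no planned figure is distorted. The missing exclusion is a gap in wording.
- **Outcome criteria displaced.** A reader might infer that the added rule overrides them. It supplements them.
- **Muscle weakness.** A reader might see a contradiction in weakness appearing as non-serious, excessive weakness as serious, and reduced strength as a result anticipated in the Discussion. The last is an expectation about measured strength, not a definition of an adverse event. Severity beyond the reference information is a plausible basis for separating the first two.
- **Caution.** Escalating unexpected and distant-spread effects is a careful choice that over-captures. With about forty patients and the nature of each effect reported, a reader could pick out mild entries by hand.

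The last point softens the consequence without removing it. The headline percentage would still carry a label that does not match its content. Caution about notification does not need the rule either, because every adverse event already requires immediate contact with the coordinator.

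**Conclusion.** The concern holds in a limited form. As written, unexpectedness is sufficient for seriousness whatever the outcome, and this conflicts with the safety analysis, which treats the two as separate. The planned number and percentage of serious effects would then not measure seriousness alone.

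The documents do not support saying that the figure fails to capture serious events, or that a safety conclusion will be reversed: no safety hypothesis or decision rule is stated. The size depends wholly on how often mild unlisted effects occur, which the article does not say, so the percentages above are conditional on the assumed rates, on their independence and on equal arms. The sample size and the analysis of the primary outcome are untouched. This is a secondary matter, but it should be corrected because it affects a planned safety figure and is cheap to put right.

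**What to change.** In Management of adverse events:
- Classify an event as serious by the outcome criteria already listed there.
- Record expectedness as a separate attribute of each effect.
- State that a non-serious event is one that does not meet the serious definition.
- State whether effects of distant spread stay in the serious class. That is for the sponsor to decide. In either case, record suspected distant spread as its own attribute.

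In Analysis of safety criteria, tabulate serious, unexpected and suspected distant-spread effects separately by arm (treatment received, as Sample analysed already specifies), so that events serious by outcome can be read on their own.

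The cost is wording in two sections and recoding of the events already recorded; twenty-eight participants had been included by 1 April 2018. Because the recoding would be done during the trial, it should be done blind to allocation and documented as an amendment. Immediate notification of the coordinator for all events stays as it is.

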## Statistical analysis

### Sample size calculation

Sample size was estimated using G*power software [59]. The input data were taken from Lampire et al. [15] who assessed the effect of BTX-A injection on length and lengthening velocity of rectus femoris during gait in chronic stroke patients). Using a two-tailed test at a threshold of 5% and a power of 80%, a sample of seventeen subjects per group was found to be necessary [60]. We therefore plan to recruit forty patients to take into account potential patients lost to follow-up. The study is currently underway. On the first of April 2018, twenty-eight participants had been included.

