### Randomization method

All patients included are routinely followed in the spasticity-units of the three participating centers. All will already be treated with BTX-A and will have undergone regular spasticity ratings using the MAS. Patients with spasticity of both the RF and TS will therefore be identified before the study is presented to them during visit 1. In addition, all patients will already have undergone routine 3D gait analysis as part of their management, thus the decrease in peak knee flexion and peak ankle plantarflexion in swing phase will already be documented, with the cause reported as RF and TS spasticity. Randomization will be carried out using randoWeb software (http://randoweb.aphp.fr) at the beginning of visit 2, then either BTX-A or the placebo will be injected according to group allocation. To avoid problems relating to expiration of the BTX-A, the BTX-A and placebo packs will be randomized, not the patients. A randomization list will be uploaded on a dedicated server (CleanWeb) and each patient will be attributed an injection pack number. The randomization will be block-balanced. Patients will thus be injected with either BTX-A or the placebo at visit 2.

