#### Analysis of primary outcome

Change in peak length of the RF and TS muscles during gait at 1 month (difference in length between V3 and V1 will be compared between groups using a Student t-test. To prevent the risk of false positives induced by multiple testing, a Bonferroni Holm correction will be applied to the *p*-values for peak length, peak force and peak strength [61]. The level of significance will be set at 0.05/3.

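### The stated 80% power is calculated at two-sided 5%, but the primary test is held to 0.05/3 within a Bonferroni-Holm procedure; at that threshold 17 per group gives about 64–68%

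*Protocol article*

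**What the plan says.** Protocol article, Sample size calculation: the requirement is stated as "Using a two-tailed test at a threshold of 5% and a power of 80%, a sample of seventeen subjects per group". The input comes from a pilot study "who assessed the effect of BTX-A injection on length and lengthening velocity of rectus femoris during gait in chronic stroke patients". No effect size, standard deviation or named test is given. The step from 34 to 40 has one stated reason: "We therefore plan to recruit forty patients to take into account potential patients lost to follow-up". Multiplicity is not mentioned.

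Protocol article, Analysis of primary outcome: the V3 minus V1 change in peak length of RF and TS is compared between groups by Student t-test. A Bonferroni-Holm correction covers the p-values for peak length, peak force and peak strength. The paragraph closes: "The level of significance will be set at 0.05/3".

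**The concern.** Both significance levels are printed in the same article and nothing reconciles them. A test held to 0.05/3 is harder to pass than one at 0.05, so a sample sized at 0.05 has less than its stated power. A reader who takes the 80% at face value could treat a non-significant result as evidence from an adequately powered trial, when the risk of missing the planned effect is larger than the protocol says.

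The figure is also narrower than the primary outcome. The outcome concerns both injected muscles, whereas the planning data concern the RF alone.

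**Working it through.** **Inputs.** From Sample size calculation: two-sided 0.05, 80% power, 17 per group, 40 in total. From Analysis of primary outcome: Student t-test, Holm over three outcomes, 0.05/3 = 0.0167. Assumed: 1:1 allocation (equal group sizes are planned, and "The randomization will be block-balanced"), and a two-sample t-test for sizing. The standardised difference d is not in the document and is back-solved.

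**Formula.** With n per group, df = 2n − 2 and noncentrality δ = d√(n/2), power = P(noncentral t with df and δ exceeds the 1 − α/2 quantile of t with df). The opposite tail is negligible.

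**Step 1: the effect that reproduces 17.** For n = 17, df = 32 and α = 0.05 the critical value is 2.037. Power of 80% needs δ = 2.889, so d = 2.889/√8.5 = 0.991. For n = 16, 80% is reached at d = 1.024. So 17 is the smallest adequate n for d from 0.991 to just under 1.024. The stated 17 is therefore internally possible, but it cannot be reproduced forward without the effect size.

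**Step 2: same effects at 0.05/3.** The critical value is 2.526 for n = 17 (df = 32) and 2.505 for n = 20 (df = 38).

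| n per group | α | Power, d = 0.991 | Power, d = 1.024 |
|---|---|---|---|
| 17 | 0.05 | 80.0% | 82.5% |
| 17 | 0.05/3 | 64.3% | 67.6% |
| 20 | 0.05 | 86.3% | 88.4% |
| 20 | 0.05/3 | 73.3% | 76.4% |

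At 0.05/3, 80% power needs 23 per group at d = 0.991 (22 at the top of the range). The effect detectable with 80% power at 0.05/3 is 1.16 SD with 17 per group and 1.06 SD with 20.

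**Step 3: full Holm step-down.** Under Holm, 0.05/3 applies to the smallest p-value; the next thresholds are 0.05/2 and 0.05. Power for peak length was simulated with three outcomes, d = 0.991 and 40,000 runs per scenario. The two values in each cell are for correlation 0 and 0.5 between outcomes.

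| Scenario | 17 per group | 20 per group |
|---|---|---|
| Only length has an effect | 65.0%, 63.8% | 73.5%, 73.3% |
| All three have d = 0.991 | 74.3%, 72.9% | 82.8%, 81.1% |

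A repeat with 100,000 runs gave 74.5% and 72.6% for the lower left cell, hence about 73–75%. Holm never tests above 0.05, so at d = 0.991 power cannot exceed the α = 0.05 values in Step 2: 80.0% at 17 and 86.3% at 20.

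**The case against.** The strongest reply is that the protocol names Bonferroni-Holm, so 0.05/3 is only the first hurdle. The protocol also expects effects on force and strength, and if those are large, peak length may be tested at 0.05/2 or 0.05. This stands in part. With all 40 analysed and three equally large effects, power is 81–83%. At 17 per group, the number the protocol calls necessary, every scenario run at d = 0.991 falls short of 80%. The Background also says that force during gait after this treatment has never been evaluated with a musculoskeletal model, so equal effects have no stated basis. The flat closing sentence on 0.05/3 does not describe a step-down rule either. If Holm-adjusted p-values were themselves compared with 0.05/3, the first hurdle would be 0.05/9 and 29 per group would be needed at d = 0.991.

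A second reply is that intention to treat with last observation carried forward keeps up to 20 per group in the analysis, so the 17-per-group figures are the pessimistic end. That is fair, and both are given. It is not a full rescue: a patient without V3 has V1 carried forward and contributes a change of zero, which dilutes the effect.

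A reader might infer more than the text supports:
- That the power is exactly 64%. The effect size is not stated, so only a range conditional on the assumed test can be given.
- That 17 is a miscalculation. It is consistent with d of about 1; the fault is the mismatch with the analysis section.
- That the false-positive rate is inflated. The stricter threshold costs power and does not raise the type I error.
- That the ethics committee was given a wrong figure. What it saw is not in this article.

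**Conclusion.** The inconsistency is real and the 80% is wrong as written for the stated decision rule. Taking 0.05/3 literally, power for RF peak length is about 64–68% with 17 per group and 73–76% with all 40 analysed. The chance of missing the planned effect is thus about 32–36% or 24–27%, against the 20% implied. Under Holm step-down at d = 0.99, power runs from about 64% to 75% at 17 per group and from about 73% to 83% at 20, depending on how strongly force and strength respond.

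These figures rest on a two-sample t-test, 1:1 allocation and a d back-solved from the stated 17. They apply to the RF only; the document gives no basis for a power figure for the TS.

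**What to change.** Keep 40 patients and make the two sections agree.

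**Restate the power.** In Sample size calculation, give the assumed d and the power at the threshold used: about 64–68% at 17 and 73–76% at 20 per group, for RF peak length. In Analysis of primary outcome, state that 0.05/3 is the first Holm step only, so that it is not read as a flat level or as a second correction on adjusted p-values. The cost is wording and a less favourable figure.

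**Alternative, by documented amendment before unblinding.** Use a fixed sequence whose first step is a single hypothesis: RF peak length at two-sided 0.05, then TS peak length, then peak force, then peak strength. Force and strength must also be ordered or split by muscle. Each test is made only if the previous one is significant. This restores the stated 80% for RF peak length with 17 per group. Starting with peak length of both muscles as one step would not secure 5% family-wise control if RF and TS are tested separately.

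The cost is that later outcomes cannot be claimed once an earlier one fails. That matters for peak strength, which Table 2 places under the first aim although the outcome section calls it secondary. With 28 participants already included by April 2018, the protocol's own rule on changes to the planned analysis requires Study Committee validation and a justified amendment.

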### Statistical analysis

Data will be analysed using SAS 9.3 (Cary Inc., NorthCarolina, USA) and “R” software (v2.14 R Foundation for Statistical Computing, Vienna,Austria. http://www.R-project.org/).

#### Description

Patients will be described by their status: eligible, included, not included (with reason for non-inclusion), left the study, and completed evaluations, within each group and for each centre (CONSORT criteria). The data will be described according to group allocation (BTX-A or placebo) and time (visit), using the usual statistics for each type of variable.

A Chi-squared test will be used to compare the distributions of qualitative variables, and analysis of variance will be used to compare the distributions of continuous quantitative variables (the variables may be adjusted to improve the symmetry or stabilise the variance). Ordinal variables (or those that do not have a normal distribution) will be compared using the non-parametric Kruskal-Wallis test.

